## Methods/design

### Trial design

The study design is a parallel-group randomised controlled trial, with 1:1 allocation. Participants with distressing persecutory beliefs who meet the inclusion criteria (see below) will be independently randomised to receive either the SlowMo intervention added to TAU, or TAU. Independent randomisation (centrally administered independently of the trial team by the King’s Clinical Trials Unit (CTU)) will use an online system generating randomly varying permuted blocks, stratified by site and baseline paranoia severity. Stratification by paranoia severity will use a median split of ≥ 62 (Green Paranoid Thoughts Scale (GPTS) part B [36] based on data from [10]). Research workers will be blind to therapy allocation, to facilitate completion of unbiased and objective assessments. Adherence to the blindness procedure will be supported by the research coordinator and therapists having responsibility for the randomisation process and informing participants of randomisation outcome. Further, the blinding procedure will be explained to participants and they will be reminded not to inform research workers of therapy allocation. Breaks in blinding will be monitored and recorded. Embedded within the design will be measures to elucidate how the treatment works. For reporting the trial, the CONSORT (Consolidated Standards of Reporting Trials; http://www.consort-statement.org/) Statement will be followed, with consideration of the mHealth evidence reporting and assessment (mERA) [37] and CONSORT-EHEALTH Checklists [38]. For the protocol, the SPIRIT (Standard Protocol Items: Recommendations for Interventional Trials [39]) Checklist and Figure are provided in this paper see: Additional file 1.

### Participants

The inclusion criteria are as follows: aged 18 years and over; persistent (3 + months) distressing paranoia (as assessed using the Schedules for Clinical Assessment in Neuropsychiatry (SCAN, [40]) and scoring > 29 on the GPTS, part B, persecutory subscale [36]; diagnosis of schizophrenia-spectrum psychosis (F20-29, ICD-10 [41]); capacity to provide informed consent; sufficient grasp of English to participate in informed consent process, assessments and interventions.

Criteria for exclusion are as follows: profound visual and/or hearing impairment; inability to engage in the assessment procedure; currently in receipt of other psychological therapy for paranoia; primary diagnosis of substance abuse disorder, personality disorder, organic syndrome or learning disability.

Mobile ownership is not a criterion for participation, as android smartphones with the SlowMo mobile app will be provided.

Participants will be recruited from mental health services across three main trial sites in England with the same procedures followed at each site: South London and Maudsley NHS Foundation Trust, Sussex Partnership NHS Foundation Trust and Oxford Health NHS Foundation Trust. Up to six additional Patient Identification Centres, comprising NHS trusts geographically near to the main recruitment trust sites, will be used as required.

### Trial flowchart

Figure 1 illustrates the trial/recruitment flowchart.

**Fig. 1 Fig1:**
[figure not shown]
SlowMo trial design and recruitment flowchart

### Planned trial interventions

SlowMo therapy consists of eight individual, face-to-face sessions, of 60–90 min, delivered by trained therapists within a 12-week timeframe, assisted by a web-based app hosted on a touchscreen laptop, with interactive personal accounts and tasks. Initial sessions involve building the meta-cognitive skill of noticing thoughts and thinking habits (visualised as bubbles spinning faster or more slowly). People learn that everyone thinks fast at times, and this can be useful. However, thinking slowly can be helpful in dealing with stress and fears about other people. This key principle frames the sessions in which people are supported to try out tips to slow down for a moment, e.g. by considering the impact of mood and past experiences on concerns and by looking for safer alternative explanations. There is an emphasis throughout the intervention on practising the skills inside and outside sessions. Participants build confidence in managing paranoia, feeling safer in their daily life and working towards a valued goal. The overall session structure is fixed, but individual content is personalised throughout as participants record their individual worries, ways of feeling safer, key learning from each session, and a message for the week ahead. All of the personalised session content is synchronised with a native mobile app installed on a standard android smartphone to assist therapy generalisation into daily life. This allows people to notice their fears and thinking habits, and supports them to slow down for a moment, by providing strategies, encouraging them to audio- or text-record helpful new information and to generate safer thoughts. Recorded information is stored in a format whereby, when experiencing recurrent concerns, people can readily access what was previously useful. Optional notifications are available if people wish the app to check-in with them. The app is specifically designed for offline use, to minimise concerns about privacy and security. Participants are not given standardised instructions about when to use the app, rather the emphasis is on tailoring usage according to what is most helpful for the individual. Use of the app is monitored objectively through data input and system analytics. Please see Fig. 2 for an overview of the main SlowMo screens.

**Fig. 2 Fig2:**
[figure not shown]
An overview of the SlowMo user interface (left: in-session digital platform; right: SlowMo app)

The development work has been done by Evolyst Ltd., a user-centred and evidence-based health care software development company. The design and development of the app has been informed by the British Standards Institute quality criteria and code of practice for health care apps (BSI; [42]). SlowMo uses a proprietary software platform developed using an Azure-based WCF (Windows Communication Foundation) Web Service, acting as an Application Programming Interface (API) to a Model View Controller (MVC) Asp.Net Web application; and a Xamarin.Android-based mobile application, allowing for use of the full Microsoft Stack and negating interoperability issues. SlowMo has currently been developed as a standalone product, given the lack of consensus on operating systems across the NHS trusts, and current interoperability issues.

TAU is care delivered to both randomised groups, according to national and local service protocols and best practice guidelines (specifically, NICE guidance on community mental health treatment for people with psychosis and the standards of community care required by the national regulators). Participation will not alter usual treatment decisions about medication and additional psychosocial interventions which remain the responsibility of the clinical team. A modified version of the Client Service Receipt Inventory [43] will be used to measure service use. Antipsychotic medication data will be extracted from medical records and dosages converted into chlorpromazine equivalents.

### Assessments and follow-up

#### Assessment of efficacy

Participants will complete a range of self-report and interview-based measures to assess the impact of the interventions on primary and secondary outcomes, the hypothesised mediators, and other key processes implicated in paranoia and response to therapy. Assessments will be completed at baseline, 12 and 24 weeks. Every effort will be made to ensure that data collection and completeness is optimised throughout the trial, and to minimise attrition/loss to follow-up. Please refer to Fig. 3 (SPIRIT Figure) for details of assessment at each visit. Assessments will be audio-taped (after first establishing consent) to allow evaluation of adherence to the research protocol and assessment ratings.

**Fig. 3 Fig3:**
[figure not shown]
Standard Protocol Items: Recommendations for Interventional Trial (SPIRIT) Figure. A digital therapy for people who fear harm from others (SlowMo): schedule of enrolment, interventions and assessments

The primary outcome is paranoia severity measured by the GPTS [36] over 24 weeks. The GPTS comprises two scales assessing thinking relevant to paranoia: ideas of social reference and persecution, rated over the preceding month. Each item is scored on a five-point Likert scale from 1 (‘not at all’) to 5 (‘totally’). A total score can be calculated ranging from 32 to 160, with higher scores reflecting higher levels of paranoia. Two 16-item subscales assess ideas of social reference (part A) and persecution (part B) relevant to paranoia.

Other paranoia outcomes:The Psychotic Symptom Rating Scales-Delusions (PSYRATS-Delusions; [44]), consisting of six items which assess the following dimensions of delusions: amount of preoccupation with delusions, duration of preoccupation with delusions, conviction, amount of distress, intensity of distress and disruption to life caused by beliefsThe persecutory delusions and ideas of reference items from the Scales for Assessment of Positive Symptoms (SAPS; [45]), a semi-structured interview designed to assess the positive symptoms of psychosis

Hypothesised mediators are measured by changes in fast thinking assessed by:Possibility of Being Mistaken (taken from the Maudsley Assessment of Delusions Schedule (MADS; [46]); Alternative Explanations from the Explanations of Experiences interview [47]). These are commonly used published methods of assessing lack of belief flexibility relating to delusional beliefsJumping to Conclusions (JTC) Beads Data-gathering Task [48] versions 85:15 and 60:40.

Please refer to Fig. 3 for details of secondary outcomes and other key processes hypothesised as moderators; these include published and established measures of wellbeing [49], quality of life [50], self and other schemas [51], service use [43], worry [52], cognitive tests [45, 53–55], other paranoia measures [56] and measures of beliefs about mental health problems and perceived relationship with carers [57, 58].

### Safety and adverse event assessment and monitoring and stopping rules

The occurrence of adverse events (AEs) will be monitored actively and systematically, following SPIRIT guidance for reporting of harms. AEs include: deaths; self-harm; serious violent incidents; complaints about therapy; and referrals to crisis care or admission to psychiatric hospital during therapy. A standard method of reporting will be employed, categorising events by severity (five grades, A–E). Subject to the approval by the independent chairperson of the Data Monitoring and Ethics Committee (DMEC, see below, ‘Research governance’), investigators will also determine whether an event is temporally related to the intervention, and whether it is unexpected or unexplained given the participant’s clinical course, previous conditions and history, and concomitant treatments. Following [59], the event will then be rated within five categories from ‘not related’ to ‘related’. Any associations between AEs and the SlowMo hardware or software will also be recorded. At each meeting of the DMEC, or at any time at the request of the DMEC chairperson, a full report of AEs will be reviewed. The DMEC will be responsible for investigating further, if there are concerns about unexpectedly high rates of AEs. This may involve the DMEC members being unblinded to the trial condition or seeking further data on AEs. If there are any ethical or safety reasons why the trial should be prematurely ended, they will advise the Trial Steering Committee (TSC) accordingly.

Individual participants will have the right to withdraw from the trial at any time. In addition the therapist, in collaboration with the participant and relevant clinical team, may decide to stop the therapy if it is directly associated with a worsening of mental state. Reasons for withdrawal from the study will be recorded. For the final reports of the trial, the numbers, types and severity of AEs by trial condition, as well as discontinuations, will be reported, using descriptive statistics (since there are no pre-specified hypotheses concerning AEs or harms, and, given the expected low frequency of AEs, the data will not be suitable for an intention-to-treat (ITT) statistical analysis).

The trial may be prematurely discontinued by the sponsor or chief investigator on the basis of new safety information or for other reasons given by the DMEC, the TSC, the regulatory authority or the Ethics Committee concerned. The trial may also be prematurely discontinued due to lack of recruitment or upon advice from the TSC, which will advise on whether to continue or discontinue the study and make a recommendation to the sponsor. If the study is prematurely discontinued, active participants will be informed and no further participant data will be collected.

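### Crisis referrals and psychiatric admissions count as adverse events only during therapy, a window that is undefined for TAU and can end at about half of follow-up in SlowMo

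*Protocol article*

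**What the plan says.** The section on safety and adverse event monitoring lists five kinds of adverse event: "AEs include: deaths; self-harm; serious violent incidents; complaints about therapy; and referrals to crisis care or admission to psychiatric hospital during therapy". For the final reports it commits to a comparison by arm: "the numbers, types and severity of AEs by trial condition, as well as discontinuations, will be reported, using descriptive statistics".

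Three other statements bear on how this list works in practice:

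- Trial design: participants are "randomised to receive either the SlowMo intervention added to TAU, or TAU". Only one arm has a trial therapy.
- Planned trial interventions: the eight SlowMo sessions are "delivered by trained therapists within a 12-week timeframe".
- Assessment of efficacy: "Assessments will be completed at baseline, 12 and 24 weeks".

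The safety section also lets the therapist, with the participant and the clinical team, stop therapy that is directly associated with a worsening of mental state. Separately, it plans a judgement of whether each event is temporally related to the intervention, followed by a five-category relatedness rating.

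**The concern.** An adverse event definition decides what is recorded while the trial runs. Here one category is tied to an exposure that only one arm has, and the resulting counts are then to be set side by side by arm. A site recording a TAU admission has no stated rule for whether it counts. A site recording a SlowMo admission in week 16, or shortly after therapy was stopped because the participant deteriorated, could properly conclude that it falls outside the definition.

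Two things are at stake for this category: whether the by-arm count is like for like, and whether events in the second half of follow-up are counted at all. A later analysis plan cannot reliably recover events that were never recorded as adverse events. The article is not silent on the window. It states one that cannot be applied equally to both arms.

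**Working it through.** **Which categories carry the limit.** Of the five listed, only crisis referral or psychiatric admission is followed by the therapy limit. Deaths, self-harm and serious violent incidents carry none. Complaints about therapy refer to therapy by their content but have no stated time limit.

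**Length of the window.**

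- SlowMo: sessions fall within 12 weeks and follow-up is 24 weeks, so the window is at most 12/24 = 50% of follow-up if therapy means the sessions.
- TAU: no trial therapy, so no window is defined. The text does not say whether this means 0, 12 or 24 weeks.

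**Illustration.** The article states no adverse event rate, so there is no figure to reproduce.

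- From the Sample size section: 60 per arm per site × 3 sites = 180 per arm.
- Assumed: the same true 24-week risk *p* of crisis referral or admission in both arms, events spread evenly over follow-up, and a SlowMo window of the first 12 weeks.
- Expected count over 24 weeks = 180 × *p*; over 12 weeks = 180 × *p* × 12/24.

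| Assumed *p* | SlowMo, 12 weeks | TAU read as 24 weeks | TAU read as no window | TAU read as 12 weeks |
|---|---|---|---|---|
| 5% | 4.5 | 9 | 0 | 4.5 |
| 10% | 9 | 18 | 0 | 9 |
| 20% | 18 | 36 | 0 | 18 |

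**Check with a constant hazard.** The 12-week risk is 1 − (1 − *p*)^0.5. At *p* = 10% this is 1 − 0.9487 = 0.0513, and 180 × 0.0513 = 9.2. At 5% and 20% the SlowMo counts are 4.6 and 19.0. The even-spread figures are close enough.

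**Reading the table.** With no true difference between arms, the wording alone can make SlowMo look about half as harmful as TAU on this item, make it look like the only arm with such events, or give equal counts that miss about half the events. No statement in the article selects among these.

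**Is the limit needed for attribution?** No. The same section already plans a separate judgement of temporal relation and a relatedness rating. Limiting the definition to the therapy period removes events before that judgement can be made.

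**The case against.** The strongest reply is that this is an ambiguity in one of five categories and not a demonstrated bias. If the period is understood as the 12-week treatment period in both arms, the counts are balanced (9 v 9 in the illustration). The zero-window reading for TAU is strained, because reporting by condition presupposes that TAU events can be counted. Both points stand, and the concern is limited accordingly. The balanced reading still drops events after week 12, and it is not written down.

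Several stronger readings are tempting and are not supported:

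- *Late harm in SlowMo goes uncounted altogether.* The limit attaches to one item only, and the list is introduced as inclusive, not exhaustive.
- *The adverse event table is the only safety comparison.* Service use is a secondary outcome, and the analysis section plans treatment-effect tests on secondary clinical outcomes. Discontinuations are also reported. The service-use inventory is not, however, linked to adverse event reporting.
- *Oversight by the Data Monitoring and Ethics Committee (DMEC) depends on this phrase.* Its chair is told of any serious adverse event as it occurs, with no therapy window, and the committee has access to all trial data. The wording about unexpectedly high rates is not stated as a between-arm trigger.
- *Complaints about therapy are a flaw in themselves.* Recording a harm specific to the intervention is reasonable, and reporting by type already makes it separable. Nor is it certain that such complaints arise only in SlowMo: "Participation will not alter usual treatment decisions about medication and additional psychosocial interventions which remain the responsibility of the clinical team", and the entry exclusion covers only people "currently in receipt of other psychological therapy for paranoia".
- *Therapy certainly ends with the sessions.* The 12 weeks apply to the sessions. The article does not say that app use stops then, or whether it counts as therapy.

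It can also be said that an article leaves collection windows to the full protocol and to a schedule figure that is not shown. That would answer a complaint that no window is given. It does not answer the point that the window given here cannot be applied to TAU.

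**Conclusion.** The point holds for one adverse event category. As written, crisis referrals and psychiatric admissions are counted over a period that is undefined for TAU and, if therapy means the sessions, is at most half of follow-up in SlowMo. The by-arm count is then either not like for like (about 9 v 18, or 9 v 0) or balanced but missing about half the events (9 v 9).

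These figures rest on an assumed 10% risk over 24 weeks, equal in both arms and evenly spread, with 180 per arm. At 5% they halve and at 20% they double. The article expects adverse events to be infrequent, so the upper end should be read with caution.

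The direction of any distortion cannot be established from the text. Deaths, self-harm and serious violent incidents are untouched. Harms are reported descriptively, so no hypothesis test, sample size or primary result is affected. What suffers is the interpretation of this line of the harms table and the completeness of its events after week 12 or after therapy is stopped.

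**What to change.** In the safety section, delete the therapy limit from the item on crisis referral and psychiatric admission. State that these events are counted from randomisation to the 24-week assessment for every randomised participant in both arms. Leave attribution to the temporal and relatedness judgements already planned. Show complaints about therapy as a line of its own, outside any between-arm adverse event total. Carry the same wording into the case report form.

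The descriptive reporting plan can stay as it is. The article justifies it by the absence of harms hypotheses and the expected low frequency, so risk differences with confidence intervals would be a preference and not a correction.

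The cost is small: a wording change and more events to record and classify. No new visits are needed, since assessments at 12 and 24 weeks are already planned. Because the sample size allows for 20% attrition, coverage to 24 weeks will be incomplete for some participants, and the number followed in each arm should be shown beside the counts.

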## Background

People often experience distressing fears about other people intentionally causing them harm: this is known as paranoia [1]. The severity of paranoia lies on a continuum, ranging from fleeting ideas that someone on the street might be laughing at us, to more elaborate and persistent beliefs (sometimes called persecutory delusions) such as that the secret services are trying to have us killed. Paranoia is one of the most common symptoms of schizophrenia-spectrum disorders, and is associated with significant distress and disruption to the person’s life [2]. This results in increased use of services, including inpatient admissions, and high costs to mental health care providers. Developing effective interventions for paranoia is, therefore, a clinical priority. The National Institute for Health and Care Excellence (NICE; 2014) recommends cognitive-behavioural therapy for psychosis (CBTp), including paranoia [3]. However, there are significant challenges to access, engagement, adherence and effectiveness [4–6]. CBTp has relatively high training and delivery costs, which limits availability. Even when it is offered, people may be reluctant to engage in therapy, and can struggle to remember what is discussed or apply new learning to daily life. Recent meta-analytical studies of CBTp have found small- to medium-sized beneficial effects on paranoia, and a pressing need to improve outcomes has been identified [6]. Our research team has approached this challenge in two main ways: firstly by adopting an *interventionist causal approach* [7] to increase CBTp effectiveness and secondly by incorporating *user-centred inclusive design methods* to enhance accessibility and usability. Our resultant new digital intervention, SlowMo, aims to improve the appeal, ease of use, memorability and clinical effectiveness of psychological therapy for people who fear harm from others.

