### Statistical analysis

We will report all participant flow, and analyses will be conducted on the ITT population: all participants will be randomised regardless of non-compliance with protocol or withdrawal from the study. Analyses will post-date final follow-up assessments, with due consideration of potential biases from loss to follow-up. The primary analysis will test for a treatment effect on the primary and secondary clinical outcomes. Random effects regression models allowing for clustering by both participants and therapists will be fitted to the repeated measures, controlling for treatment site, baseline paranoia severity and the corresponding baseline assessment for the outcome under investigation. We will allow for missing outcome data under the Missing At Random assumption [60]; we may also use inverse probability weighting to adjust for non-adherence to allocated treatment and other intermediate outcomes as predictors of future loss to follow-up [61]. Secondary analyses will test treatment-effect mechanisms, moderation and process/adherence effects using modern causal inference methods [62, 63]. The trial outcomes will comprise two parallel series of longitudinal data: one for the putative mediators (M) and one for the clinical outcomes (Y).

For the mechanistic analysis, to test for a treatment effect on the putative mediator, we will replace the clinical outcome with the mechanistic variable as the dependent variable in the random-effect models. If we separately demonstrate a treatment effect on both the putative mediator and on the clinical outcome, we will evaluate mediation in these parallel longitudinal data sets through the use of parallel growth curve and latent change models [64, 65]. These models preserve the basic mediation model by replacing observed variables with latent constructs – the growth factors driving the temporal responses, M_1_ to M_p_ and Y_1_ to Y_p_. Importantly, the mediational structure only applies to the slope growth or change factors since randomised treatments are independent of the intercept growth factors (baseline values). Growth curve and latent change models can be estimated by maximum likelihood and other methods using the software package Mplus [66]. The application of these methods to mechanism evaluation within EME (Efficacy and Mechanism Evaluation) trials is illustrated in [62]

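### Expected rarity of adverse events is no reason to set aside intention-to-treat: harms can be reported as randomised, with an interval and without a test

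*Protocol article*

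**What the plan says.** The safety section of the Protocol article (Safety and adverse event assessment and monitoring and stopping rules) plans that "the numbers, types and severity of AEs by trial condition, as well as discontinuations, will be reported, using descriptive statistics". It gives two reasons. The first is "since there are no pre-specified hypotheses concerning AEs or harms". The second is that, "given the expected low frequency of AEs, the data will not be suitable for an intention-to-treat (ITT) statistical analysis". No expected AE rate or count is given there or elsewhere in the article.

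The AE list in the same section includes deaths, self-harm and serious violent incidents, and also "complaints about therapy" and "referrals to crisis care or admission to psychiatric hospital during therapy".

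For the trial's analyses in general, the Statistical analysis section says that "analyses will be conducted on the ITT population".

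**The concern.** The second reason treats intention-to-treat as if it were a kind of significance test that needs enough events to run. It is a rule about the analysis set: everyone randomised, in the arm to which they were randomised. The rule applies equally to 2 events and to 200.

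This is a stated position, not a detail left for later. Taken literally, it declares the harms data unfit for the as-randomised comparison and names no other population. It also offers rarity as grounds for giving no between-arm estimate. Counts by arm, with nothing to show their precision, are easily read as evidence of no difference when the numbers are small. For a new therapy in people with severe mental health difficulties, readers need to see how large a difference in harms the trial could not exclude.

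A related problem affects any between-arm comparison. At least the crisis-care and admission items are tied to the period of therapy, and one item concerns complaints about therapy. The treatment-as-usual (TAU) arm has no trial therapy, so the article defines no counterpart for either.

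**Working it through.** **Inputs.** From Sample size: 360 participants, 1:1 allocation, so 180 per arm. From Planned trial interventions: therapy within 12 weeks. From Assessments and follow-up: assessments at baseline, 12 and 24 weeks. The article states no AE rate, so there is no harms figure to reproduce. The rates below (1% to 20% of participants with at least one event, equal in both arms) are assumptions chosen to span rare to common.

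**Step 1: can an as-randomised estimate with an interval be computed when events are rare?** The simple (Wald) 95% half-width for the risk difference is 1.96 × √(2p(1 − p)/180). At p = 0.02 this is 1.96 × √(0.0392/180) = 1.96 × 0.01476 = 0.029. At p = 0.10 it is 1.96 × √(0.18/180) = 1.96 × 0.03162 = 0.062.

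Wald intervals are too narrow with few events, so the Newcombe interval was computed as well, at the nearest whole number of events. With 4 of 180 in each arm, the Wilson limits for each proportion are 0.0087 and 0.0557 around 0.0222. The half-width is √((0.0222 − 0.0087)² + (0.0557 − 0.0222)²) = 0.036.

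**Step 2: what does rarity do to a test?** The power to detect a doubling from p₁ to p₂ = 2p₁ (two-sided 5%, normal approximation, p̄ the mean of the two rates) is Φ{[(p₂ − p₁) − 1.96√(2p̄(1 − p̄)/180)] / √([p₁(1 − p₁) + p₂(1 − p₂)]/180)}. For 5% against 10% this is Φ[(0.05 − 1.96 × 0.02776)/0.02764] = Φ(−0.16) = 0.44.

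| Assumed rate | Expected participants with an event, per arm | Wald half-width (points) | Newcombe half-width (points; events per arm) | Power to detect a doubling |
|---|---|---|---|---|
| 1% | 1.8 | 2.1 | 3.0 (2) | 12% |
| 2% | 3.6 | 2.9 | 3.6 (4) | 20% |
| 5% | 9 | 4.5 | 4.8 (9) | 44% |
| 10% | 18 | 6.2 | 6.4 (18) | 76% |
| 20% | 36 | 8.3 | 8.3 (36) | 99% |

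**Step 3: no events in one arm.** The exact two-sided 95% upper limit is 1 − 0.025^(1/180) = 0.020, or 2.0%.

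**Reading.** An interval exists in every row and also at zero events. Only the last column deteriorates as events become rare. Rarity is therefore an argument against testing, not against counting by randomised arm or giving an interval.

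The half-widths ignore clustering by therapist. If the ICC of 0.01 that Sample size uses for the paranoia score also applied to AEs (an assumption), 18 participants per therapist (180/10) would give a design effect of 1 + 17 × 0.01 = 1.17 in the SlowMo arm. The half-widths would then be wider by √((1 + 1.17)/2) = 1.04, about 4%.

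**The case against.** The strongest reply is that the section gives an independent and common reason for descriptive reporting: no harms hypotheses were set. That stands, and it is why no test is asked for here. It does not cover the second reason, which is about rarity and is wrong on its own terms.

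A second reply is that the phrase is loose wording for an inferential comparison, and that reporting by trial condition most naturally means by randomised arm. This is probably what was meant. It limits the point to a mistaken rationale and a missing interval. Descriptive statistics could include a risk difference, a reader could derive a crude one from counts of participants, and an analysis plan not shown might specify one. But an analysis plan that set out an as-randomised analysis would then be at odds with this sentence, which is reason enough to correct it.

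Three stronger readings are tempting, and the article does not support them:

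- **That AEs will in fact be common.** The Background says of paranoia: "This results in increased use of services, including inpatient admissions". The AE list does include crisis referrals and admissions. But that remark is qualitative, with no rate, period or comparator, and those AE items are limited to therapy, which is planned within 12 weeks. The expectation of low frequency is unsupported, not refuted. The section also provides for the monitoring committee to investigate unexpectedly high rates.
- **That the safety section contradicts the Statistical analysis section.** The general intention-to-treat statement introduces the efficacy, mechanism, moderation and adherence analyses. The two sections are in tension, no more.
- **That the SlowMo harms rate will be biased downwards because the denominator is therapy starters or completers.** Nothing restricts the denominator in that way. Discontinuations are to be reported by arm and reasons for withdrawal recorded, so early leavers would be visible.

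**Conclusion.** The point holds in a limited form. The lack of harms hypotheses justifies omitting tests. The claim that low frequency makes the data unsuitable for intention-to-treat is incorrect and has no figure behind it. With 180 per arm, an as-randomised risk difference can be given with a 95% half-width of about 3 to 4 points at 2% (Wald 2.9, Newcombe 3.6), 4.5 at 5%, 6.2 at 10% and 8.3 at 20%; the last three are Wald values, with Newcombe at 4.8, 6.4 and 8.3. With no events in an arm, the upper limit is about 2.0%.

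These sizes rest on assumed, equal rates in the two arms, full recruitment and no therapist clustering. The conclusion that rarity is no bar rests on none of them. No efficacy conclusion is affected. What changes is whether the harms report shows its own imprecision.

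**What to change.** Delete the clause saying that the data are unsuitable for an intention-to-treat analysis, and keep the statement that no harms hypotheses are pre-specified as the reason for not testing. Then state the following:

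- For any AE and for each AE category except complaints about therapy, report the number of events and the number of participants with at least one event, by randomised arm, with all randomised participants as the denominator.
- Count events over one window that starts at randomisation and is the same in both arms (the assessment schedule offers 12 or 24 weeks), in place of a window tied to therapy.
- Give the risk difference with a 95% interval suited to sparse data (exact or Miettinen-Nurminen), without hypothesis tests.
- Report complaints about therapy for the SlowMo arm only, since TAU has no counterpart.

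The cost is a change of wording and one extra table. The intervals will be wide, which states openly how little the trial can exclude. An all-randomised denominator also counts participants lost early as event-free unless their events are found by other means, so the table should show how many in each arm were observed for the whole window.
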